**Step 2**	
Patients should not enter the study if any of the exclusion criteria from STEP 1 and the following criteria for STEP 2 are fulfilled: 26 Patient with progression observed on CT scan performed after 6 weeks of olaparib (STEP 1).	

^a^ Except alopecia, ototoxicity, vitiligo, and laboratory values defined in inclusion criteria. Patients with Grade ≥ 2 neuropathy will be evaluated on a case-by-case basis after consultation with study physician. Patients with irreversible toxicity not reasonably expected to be exacerbated by treatment with olaparib or durvalumab or tremelimumab may be included only after consultation with study physician

^b^ Concurrent use of hormonal therapy for non–cancer-related conditions (e.g., hormone replacement therapy) is acceptable

^c^ Non-palliative radiotherapy within 21 days prior the first dose of study drug or within 6 weeks for therapeutic doses of MIBG or craniospinal irradiation. Palliative radiotherapy (which would be < 30% of the bone marrow) to non-target lesions is allowed

^d^ Patient with allogenic stem cell transplant within 3 months prior the first study dose of Olaparib are not eligible. Patient with myeloablative therapy with autologous hematopoietic stem cell rescue within 8 weeks of the first study drug dose are not eligible. Patients receiving any agent to treat or prevent graft-versus host disease ‘GVHD) post bone marrow transplant are not eligible for this trial

^e^ Except for: malignancy treated with curative intent and with no known active disease ≥5 years before the first dose of IP and of low potential risk for recurrence; adequately treated non-melanoma skin cancer or lentigo maligna without evidence of disease; adequately treated carcinoma in situ without evidence of disease and history of leptomeningeal carcinomatosis

### Investigational products

Olaparib, durvalumab and tremelimumab will be supplied by AstraZeneca.

### Study procedures

All patients respecting all eligibility criteria, namely presenting mutations in homologous repair genes will be included. Regimens sequence is presented in Fig. 1. Study will be divided into two successive steps:
*Step 1*After 6-weeks of olaparib, all patients from STEP 1 will have a CT scan.*Step 2*Depending on CT scan results, two situations will occur:
Patients with stable disease or partial response will follow olaparib + immunotherapy by durvalumab + tremelimumab during 4 months and then continue with durvalumab alone until progression or until 24 dosing maximum of durvalumab for all cohorts except for ovarian cohort with a maximum of 36 dosing.Patient with progression will be withdrawn from the study and treated according to standard care.

#### Ancillary studies

Ancillary studies will be conducted to evaluate the immunogenic effect of study treatments. Before any procedure, patients should consent to participate to the exploratory studies by signing a specific informed consent form.

### Treatment doses and regimens

#### Olaparib

Patients will be administered olaparib study treatment tablets orally at a dose of 300 mg bid.

The maximum duration of treatment with olaparib is 8 weeks, corresponding to the duration of STEP 1, + 4 months, the duration of the initial part of STEP 2. The initial dose of 300 mg bid will be made up of 2 × 150 mg tablets bid. All doses of study treatment should be taken at the same time every day approximately 12 h apart.

#### Durvalumab + tremelimumab combination therapy

Patients in the durvalumab + tremelimumab combination therapy treatment will receive durvalumab (1500 mg Q4W) in combination with tremelimumab (75 mg IV Q4W) for up to 4 doses/cycles each, followed by durvalumab 1500 mg Q4W until confirmed PD (progressive disease), unacceptable toxicity, consent withdrawal, or occurrence of events leading to treatment discontinuation. With a maximum of 24 dosing of durvalumab (36 dosing for ovarian cohort).

Tremelimumab will be administered first. Durvalumab infusion will start approximately 1 h (maximum 2 h) after the end of the tremelimumab infusion. Standard infusion time for each is 1 h.

The first durvalumab monotherapy dose at 1500 mg Q4W will be 4 weeks after the final dose of durvalumab in combination with tremelimumab. (Cycle 5). After 20 cycles, durvalumab will be stopped for all cohorts, except for the ovarian cohort for a maximum of 32 months with durvalumab.

All patients will be followed for disease progression and survival until 24 months after the end of treatment.

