### Study endpoints

The primary endpoint is progression free survival (PFS) 6 months after the initiation of immunotherapy for all cohorts, with the exception of ovarian cohort evaluated at 12 months. PFS is defined as the time from the date of first dose of immunotherapy to the date of progression or death from any cause. Progression will be defined using iRECIST criteria.

Secondary endpoints are:
Disease control rate, including stable and responsive disease, evaluated 6 months after immunotherapy initiation for all cohorts except ovarian cohort, evaluated at 12 months.Overall survival (OS) evaluated at 12 and 24 months after immunotherapy initiation defined by the time of the first immunotherapy dose to the date of death from any cause.Response rate evaluated by CT scan, RECIST evaluation after 6 weeks of olaparib therapy.Olaparib toxicity evaluated at the end of STEP1 using CTCAE V5.Olaparib + immunotherapy (tremelimumab + durvalumab) toxicity evaluated at 3, 6 and 12 months after immunotherapy initiation using CTCAE V5.

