### Treatment duration and criteria for retreatment

Treatments will be administered on Day 1 for up to 4 months for olaparib + durvalumab + tremelimumab and then from day 1 of month 5 for up to day 1 of month 24 (all cohorts) or month 36 (only for ovarian cohort) for durvalumab alone or until confirmed PD, unacceptable toxicity, consent withdrawal or occurrence of events leading to treatment discontinuation (Fig. 2). Patient will have a maximum of 24 doses of durvalumab, except for ovarian cohort that will reach a maximum of 36.

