### Withdrawal and discontinuation criteria

At any time, subjects are free to withdraw from the study (investigational product and assessments), without prejudice of further treatment (withdrawal of consent). The reason(s) for withdrawal and the presence of any AEs will be investigated.

Patients who withdraw consent for further participation will not receive any further investigational product or further study observation, with the exception of follow-up for survival, which will continue until the end of the study unless the patient has expressly withdrawn his or her consent to survival follow-up.

Subject will be considered lost to follow-up only if no contact has been established by the time the study is completed such that there is insufficient information to determine the subject’s status at the time.

Reasons that will lead to permanent investigational product discontinuation are detailed in Table 3. Any patient who has not yet shown objective radiological disease progression at withdrawal from investigational product should continue to be followed as per RECIST 1.1.

**Table 3 Tab3:** Criteria for permanent discontinuation of investigational product

Discontinuation criteria - Investigational product	
1 Patient weight falls to 30 kg or less.	
2 Withdrawal of consent to participate in the study or lost to follow-up.	
3 Withdrawal of consent for further treatment with investigational product.	
4 Adverse event that, in the opinion of the investigator or the sponsor, contraindicates further dosing.	
5 Patient who will probably meet one or more exclusion criteria at study entry, to whom pursuing investigational therapy might constitute a safety risk.	
6 Pregnancy or intent to become pregnant.	
7 Any AE that meets discontinuation criteria.	
8 Grade ≥ 3 infusion reaction to durvalumab or tremelimumab.	
9 Patient non-compliance that, in the opinion of the investigator or sponsor, warrants withdrawal.	
10 Initiation of alternative anticancer therapy including another investigational agent.	
11 Confirmation of PD and no benefit from treatment with olaparib or durvalumab + tremelimumab.	
12 Bone marrow findings consistent with MDS/AML.	

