#### Analysis of efficacy endpoint(s)

Efficacy analyses will be performed in modified intent-to-treat population (ITT) population ie, all patients with a 6-month evaluation (12-month for ovarian cohort) and at least one dose of durvalumab + tremelimumab. Analyses will be repeated in the per protocol population (patients who had received all the planned doses).

6-month PFS rate (12 month-rate in the ovarian cohort) will be determined using the Kaplan Meier method. 95% Confidence interval (CI) will be provided. Patients alive without progression will be censored.

Median follow-up will be estimated using the reverse Kaplan Meier method.

PFS and Overall survival will be estimated using the Kaplan Meier method. Six-month, 1-year, 2-year rates as well as median OS and PFS will be reported with their 95% CI.

Disease control rates at 6 months will be determined and described with its 95% binomial CI. The same method will be applied to describe the response rate after 6 months of olaparib in each cohort.

All statistical analysis will be performed with SAS 9.4. In case of comparison, tests will be two-sided.

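### Survival follow-up tied to the end of treatment makes censoring informative after month 24, so any median OS beyond 24 months is biased upward

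*Protocol article*

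**What the plan says.** All references are to the protocol article.

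- **Origin and time points** (Study endpoints): "Overall survival (OS) evaluated at 12 and 24 months after immunotherapy initiation defined by the time of the first immunotherapy dose".
- **End of treatment** (Durvalumab + tremelimumab combination therapy): "followed by durvalumab 1500 mg Q4W until confirmed PD (progressive disease), unacceptable toxicity, consent withdrawal, or occurrence of events leading to treatment discontinuation". The section on treatment duration and retreatment adds a ceiling: "Patient will have a maximum of 24 doses of durvalumab, except for ovarian cohort that will reach a maximum of 36".
- **End of follow-up** (Durvalumab + tremelimumab combination therapy): "All patients will be followed for disease progression and survival until 24 months after the end of treatment".
- **Estimator and summaries** (Analysis of efficacy endpoint(s)): "PFS and Overall survival will be estimated using the Kaplan Meier method". Also: "Six-month, 1-year, 2-year rates as well as median OS and PFS will be reported with their 95% CI".
- **Patients who withdraw consent** (Withdrawal and discontinuation criteria): they receive no further product or observation, "with the exception of follow-up for survival, which will continue until the end of the study", unless they also refuse survival follow-up.

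The Statistical analyses section adds that each cohort is analysed separately, so a median OS is promised for each one.

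**The concern.** Kaplan-Meier assumes that a patient censored at month t has the same later death rate as those still observed. Here the censoring time depends on how long the patient stayed on treatment, and that depends mainly on when the disease progressed. A patient who stops at month 2 and is still alive leaves observation at month 26. A patient treated for 24 months is observed to month 48. Those who leave early have already progressed, so their death rate is higher than that of the patients who remain, and the late part of the curve sits too high.

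This is a single-arm trial, so readers will set each cohort's median OS beside outside figures. An error that always favours the treatment matters in that comparison. In addition, the article uses two different ends of survival follow-up: end of treatment plus 24 months for all patients, and the end of the study for those who withdraw consent.

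**Working it through.** **Step 1: who is observed when.** Let T be time on treatment, measured from the first immunotherapy dose. Read per patient, the censoring time is C = T + 24 months.

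- T cannot be negative, so C is at least 24. Every patient is covered to month 24.
- After month 24, a living patient is observed at month t only if T > t − 24. At month 30 this means treated for more than 6 months; at month 36, more than 12.
- The longest T follows from the dose ceiling. 24 doses every 4 weeks span 23 × 28 = 644 days, or 21.2 months; 36 doses span 35 × 28 = 980 days, or 32.2 months. In the ovarian cohort, observation would then end by about 32.2 + 24 = 56.2 months.

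**Step 2: size.** The article gives no PFS or OS figure to reproduce, so all survival inputs below are assumptions. Each scenario simulates 400,000 patients:

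- PFS is exponential, and OS = PFS + exponential post-progression survival.
- T = min(PFS, 24 months), or min(PFS, 36 months) for the ovarian-like rows.
- C = T + 24, and the Kaplan-Meier median is compared with the uncensored truth.
- Shared prognosis means a gamma frailty of variance 0.3 acting on both PFS and post-progression survival.

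| Median PFS / post-progression survival (months) | Shared prognosis | True median OS | Kaplan-Meier median | Difference |
|---|---|---|---|---|
| 6 / 24 | no | 33.6 | 34.0 | +0.4 |
| 6 / 24 | yes | 37.6 | 41.4 | +3.8 |
| 12 / 18 (ovarian-like) | no | 36.0 | 37.1 | +1.1 |
| 12 / 24 (ovarian-like) | no | 42.5 | 44.9 | +2.4 |
| 12 / 30 (ovarian-like) | no | 48.9 | 52.9 | +4.0 |
| 12 / 24 (ovarian-like) | yes | 47.3 | 56.0 | +8.7 |

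A second set of scenarios used treatment spans of 21.2 and 32.2 months, toxicity stops of 0 or 2% per month, and a frailty SD of 0 or 0.7. It gave:

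- 0.0 months at true medians of 11.5 to 19.1 months;
- +0.1 to +0.2 at about 27 to 28 months;
- +1.1 to +3.2 at about 35 to 38 months;
- +3.2 to +4.4 at about 42 to 44 months;
- median not reached at about 50 to 52 months.

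**Step 3: where the curve departs.** For 12 / 18 months without shared prognosis, Kaplan-Meier and true OS agree at month 24 (0.690 and 0.690). They then separate: 0.513 against 0.499 at month 36, and 0.443 against 0.417 at month 42.

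**Step 4: is the ovarian dose ceiling the cause?** No. In the 12 / 18 scenarios, cutting the span from 32.2 to 21.2 months left the bias at +1.1 to +1.7, against +1.1 to +1.6. In the 12 / 24 scenario, capping treatment at 24 months gave 45.1 against a true 42.6 (+2.5).

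**Step 5: PFS.** A patient who stops at progression already has the PFS event. With independent toxicity stops of 2% per month, the estimated PFS at 24, 30 and 36 months equalled the truth (0.250, 0.176, 0.125).

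**The case against.** **The endpoint as defined is safe.** OS is named at 12 and 24 months, and both rates are unbiased. This stands. Only the later curve and the promised median are exposed, and the median only where it exceeds 24 months.

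**The per-patient reading is not written.** The article does not say whose end of treatment is meant. Following patients who withdraw longer than those who stay would be odd, so a study-level end may be intended, and the full protocol may say so. That is possible. But treatment ends on a different date for each patient, so the per-patient reading is the natural one, and the two passages still need reconciling.

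**Retreatment lengthens time on treatment.** It does, and the simulations above leave it out. With an assumed 30 to 60% uptake among eligible progressors, ovarian-like biases of +2.5 and +4.1 months fall to +2.2 to +1.9 and +3.4 to +2.9. Most of the bias remains.

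**Precision swamps it.** Cohort sizes are not given. Assuming 24 to 60 patients in the 12 / 24 scenario, the interquartile range of the estimated median runs from about 38–56 to about 40–51 months, against a bias of about 2.5. This is fair, and it limits the weight of the point. The error is still systematic and always in the same direction.

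**Stronger readings that the documents do not support.**

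- *A reader might infer that only long-treated patients remain after two years.* At month 30 only those treated for under 6 months have left, and in the ovarian-like scenarios 62 to 75% of living patients are still observed at month 36.
- *A reader might infer that the ovarian cohort is worst affected because of its 36 doses.* Step 4 shows that the ceiling is not the driver. A longer OS would be, and the article gives no OS for any cohort.
- *A reader might take the bias to be about 9 months.* That is one shared-prognosis scenario. Its estimate of 56.0 lies at the very end of the 56.2 months of possible observation, so the likely report is a median not reached.

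**Conclusion.** The point holds in a limited form. On the per-patient reading, the follow-up rule makes OS censoring informative after month 24, and the plain Kaplan-Meier median is biased upward in any cohort whose median OS exceeds 24 months.

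Without shared prognosis, the bias is about 0 for true medians below 24 months, under 0.5 months at about 27 to 34 months, and about 1 to 4 months at about 36 to 49 months. With shared prognosis it is larger, or the median is not reached. These sizes rest wholly on assumed survival. The direction, and the absence of bias up to month 24, follow from the rule itself, given that treatment ends mainly at progression.

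This is a worthwhile, inexpensive correction to a secondary result. It does not touch the primary PFS endpoint or the 12- and 24-month OS rates, and nothing in the documents shows a problem with the PFS analysis.

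**What to change.** Choose one, and state the same rule in the sections on combination therapy, on withdrawal and on efficacy analysis.

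1. **Common cut-off.** Collect vital status for all STEP 2 patients to one study cut-off date and censor OS there, in place of end of treatment plus 24 months. This also brings the general rule into line with the one for patients who withdraw consent. Cost: vital-status checks on patients who stopped early, so it must be decided while they can still be traced.
2. **Truncation.** Censor OS at 24 months from the first immunotherapy dose, the time to which every patient is covered, and report a median only if it is reached by then. Cost: wording only, but the median may be not reached in cohorts with long survival.

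Under either option, keep the 12- and 24-month OS rates and leave the PFS analysis as it is; truncating PFS would discard valid data.

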### Treatment duration and criteria for retreatment

Treatments will be administered on Day 1 for up to 4 months for olaparib + durvalumab + tremelimumab and then from day 1 of month 5 for up to day 1 of month 24 (all cohorts) or month 36 (only for ovarian cohort) for durvalumab alone or until confirmed PD, unacceptable toxicity, consent withdrawal or occurrence of events leading to treatment discontinuation (Fig. 2). Patient will have a maximum of 24 doses of durvalumab, except for ovarian cohort that will reach a maximum of 36.

**Fig. 2 Fig2:**
[figure not shown]
Olaparib + durvalumab + tremelimumab combination therapy dosing schedule

Patients with rapid tumor progression or with symptomatic progression requiring urgent medical intervention will not be eligible to continue durvalumab ± tremelimumab treatment.

For all patients who are treated through progression or patients who achieve disease control [i.e., CR, PR, or SD] at 12 months and restart treatment upon evidence of PD during follow-up, the investigator should evaluate whether patients have any significant, unacceptable or irreversible toxicities that might indicate that continuing or restarting treatment would not further benefit the patient. Patients who progressed during the first 4 months, during combination of durvalumab and tremelimumab are not allowed to be retreated.

Patients meeting the retreatment criteria below, will respect the same treatment guidelines followed during the initial 12-month treatment period, including the same dose and treatment frequency of durvalumab + tremelimumab without olaparib and the same schedule of assessments. The only exception will be the ancillary study, tumor biopsies won’t need to be collected a second time.

Patients who meet the criteria for retreatment may only receive retreatment once.
Patients may not undergo retreatment if:Patients have evidence of PD during the portion of the regimen concerning the combination period of durvalumab + tremelimumab. Olaparib will not be restarted.Patients may undergo retreatment as described below:
Patients who complete the 4 dosing cycles of the combination olaparib + durvalumab and tremelimumab portion of the regimen (with clinical benefit per Investigator judgment), but subsequently have evidence of PD during the durvalumab monotherapy, with or without confirmation according to RECIST 1.1, may restart treatment with the combination, if there are 4 months between last cycle of first combination treatment and progression.Patients who achieve and maintain disease control (i.e., CR, PR, or SD) through to the end of the 12-month treatment period may continue treatment with durvalumab alone until evidence of PD, with or without confirmation and according to RECIST 1.1, during follow-up.

For all patients who restart treatment with the combination as well as patients who continue Durvalumab alone, the investigator should ensure:
Patients do not have any significant, unacceptable, or irreversible toxicities that might indicate that continuing treatment would not further benefit the patient.Absence of clinical symptoms or signs indicating clinically significant disease progression accompanied by a decline in WHO/ECOG performance status to > 1.Absence of rapid disease progression or threat to vital organs or critical anatomical sites requiring urgent alternative medical intervention.Patient still fulfills eligibility criteria for this study. Patients must also agree to fill an additional consent to restart durvalumab + tremelimumab combination therapy.If applicable, retreatment will be possible:

During the retreatment period, patients in the durvalumab + tremelimumab combination therapy group will resume durvalumab dosing at 1500 mg Q4W with 75 mg of tremelimumab Q4W for 4 doses/cycles each. Patients will then continue with durvalumab monotherapy at 1500 mg Q4W, beginning at Week 16, 4 weeks after the last dose of combination therapy, until disease progression or up to a total of 9 additional doses/cycles with the final dose at Week 48 (Month 12). Olaparib will not be restarted.

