21 Current or prior use of immunosuppressive medication within 14 days before inclusion.	
22 Administration of live attenuated vaccine within 30 days prior to the first dose of IP.	
23 Female patients who are pregnant or breastfeeding or male or female patients of reproductive potential not willing to employ effective birth control.	
24 Known allergy or hypersensitivity to any of the study drugs or excipients.	
25 Prior treatment with any PARP inhibitor including olaparib or immunotherapy.	

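### The retreatment text assumes a 12-month initial course, but the regimen elsewhere runs to 24 durvalumab doses (36 ovarian); the rules conflict after Week 48

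*Protocol article*

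**What the plan says.** The initial regimen is described in four places.

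- The Abstract (Methods) limits treatment to 24 months, or 36 in the ovarian cohort.
- Study procedures gives durvalumab alone after the combination "until 24 dosing maximum of durvalumab for all cohorts except for ovarian cohort with a maximum of 36 dosing".
- Durvalumab + tremelimumab combination therapy sets up to four combination cycles and then says: "After 20 cycles, durvalumab will be stopped for all cohorts, except for the ovarian cohort for a maximum of 32 months with durvalumab".
- Treatment duration and criteria for retreatment schedules monotherapy "from day 1 of month 5 for up to day 1 of month 24 (all cohorts) or month 36 (only for ovarian cohort", and adds: "Patient will have a maximum of 24 doses of durvalumab, except for ovarian cohort that will reach a maximum of 36".

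Further on in that last section, in the text after Fig. 2, the initial treatment period is said to last 12 months. One sentence there has patients with disease control at 12 months restarting treatment if they progress in follow-up. A later bullet says that patients who keep disease control "through to the end of the 12-month treatment period may continue treatment with durvalumab alone until evidence of PD".

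Retreatment is allowed once. It consists of four combination cycles, then durvalumab alone from Week 16 "until disease progression or up to a total of 9 additional doses/cycles with the final dose at Week 48 (Month 12". Restarting and continuing durvalumab alone are both subject to a list of conditions, one of which reads: "Patient still fulfills eligibility criteria for this study". Exclusion criterion 25 in Table 2, listed under Step 1, reads: "Prior treatment with any PARP inhibitor including olaparib or immunotherapy".

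**The concern.** A restart on progression in follow-up presupposes that treatment had stopped at 12 months. Permission to continue presupposes a decision point at 12 months. The 24/36-dose schedule has neither: under it, month 12 falls in the middle of scheduled monotherapy. After Week 48 a site could therefore take durvalumab as scheduled up to the maximum, as stopped and restarted on progression, or as optional and subject to fresh conditions.

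Four things in the article depend on which reading is used:

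- Cumulative exposure to the two immunotherapies, and the safety summaries that cover it.
- PFS and OS at 2 years, which could pool patients treated for different lengths of time under one protocol.
- The end of follow-up, which the combination therapy section sets at 24 months after treatment ends.
- The per-protocol population in Analysis of efficacy endpoint(s), which is limited to patients who received every planned dose. The number planned is not the same under the two descriptions.

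A separate question is whether a retreatment course counts toward the 24/36 maximum. The article gives both limits without relating them.

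**Working it through.** The check is a dose count on a four-weekly grid with the first dose at week 0. A month in the dosing text is read as one four-week cycle.

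**1. The stated regimen.** Four combination cycles plus 20 monotherapy cycles: 4 + 20 = 24. Ovarian cohort: 4 + 32 = 36. Both reproduce the stated maxima. The last dose falls at week 4 × 23 = 92, or at week 4 × 35 = 140 in the ovarian cohort.

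**2. The 12-month course.** Combination doses fall at weeks 0, 4, 8 and 12 (4 doses). Monotherapy at weeks 16, 20, …, 48 gives (48 − 16)/4 + 1 = 9 doses. The total is 13. This is the retreatment schedule as written, and a 12-month initial period on the same grid holds the same 13 doses.

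**3. Where the descriptions part.** They coincide through Week 48. After it, 24 − 13 = 11 doses (36 − 13 = 23 ovarian) are scheduled in one place and conditional in the other. For a patient who completes treatment, its end moves by 92 − 48 = 44 weeks (140 − 48 = 92 weeks ovarian), and the end of follow-up moves with it.

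**4. Retreatment against the maximum.** With k initial doses and a full retreatment course, the total is k + 13.

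| Cohort | k | Total | Stated maximum |
|---|---|---|---|
| Non-ovarian | 11 | 24 | 24 |
| Non-ovarian | 12 | 25 | 24 |
| Non-ovarian | 13 | 26 | 24 |
| Non-ovarian | 24 | 37 | 24 |
| Ovarian | 23 | 36 | 36 |
| Ovarian | 24 | 37 | 36 |
| Ovarian | 36 | 49 | 36 |

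A full course passes the maximum from k = 12, or from k = 24 in the ovarian cohort. Whether that breaks a rule depends on whether the maximum covers retreatment, which is not stated.

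**5. Reach into the primary endpoint.** Six calendar months are 6 × 365.25/12/7 = 26.1 weeks, which is before Week 48. Retreatment after progression on monotherapy requires four months since the last combination cycle. Counting from dose 4 at week 12, the earliest qualifying progression is at week 12 + 16 = 28 with four-week months, or 12 + 17.4 = 29.4 with calendar months. Both fall after week 26.1. Neither the length conflict nor retreatment touches the 6-month endpoint of the non-ovarian cohorts.

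**6. Eligibility at retreatment.** Every retreatment candidate has had olaparib, durvalumab and tremelimumab in the study. The condition that eligibility still be met does not exempt study treatment from exclusion 25, and it applies equally to patients who only continue durvalumab.

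**The case against.** The strongest reply is that the regimen is clear. Four places agree on it, the cycle counts add up, and the 12-month wording appears only in the retreatment text. This is also a condensed article whose dosing figure is not shown, so the counting rule and the list of re-checked criteria may stand in the full protocol. The first part limits the point: the treatment is uniquely described up to Week 48. The second part does not remove it, because the article contradicts itself on the initial period and does not merely omit detail.

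Four stronger readings are tempting, and the document does not support them.

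- **Durvalumab has no cap after 12 months.** This is inferred from silence. The same section has just set the maximum, and the sentence on continuing does not lift it.
- **A patient who restarts after 12 months receives at least 26 doses.** This treats a ceiling as a floor. Retreatment monotherapy stops at progression, so 26 is reached only with 13 initial doses and a full second course.
- **Nobody can qualify for retreatment.** Exclusion 25 is a Step 1 criterion and evidently concerns treatment before study entry. Table 2 also re-applies all Step 1 exclusions at Step 2, when every patient has had olaparib, so the literal reading would empty Step 2 as well. What remains is a missing exemption.
- **The 12-month results or the primary endpoint mix treatment lengths.** The schedules are identical to Week 48, so 12-month PFS does not mix them. An effect on the ovarian primary endpoint through treatment length would need the 18-month assessment named in Sample size calculation. Study endpoints gives 12 months, and that discrepancy is a separate matter.

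**Conclusion.** The concern holds in a limited form. The 12-month initial period in the retreatment text cannot be the same course as the 24/36-dose regimen described elsewhere, and the rules conflict after Week 48 over 11 doses (23 ovarian). Separately, a retreatment course of up to 13 doses can take the durvalumab total above 24 (36 ovarian), to at most 37 (49 ovarian) if the two limits are separate. The article does not say which applies. The eligibility condition is a secondary wording defect.

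The consequences lie in late treatment, cumulative exposure, 2-year PFS and OS, the end of follow-up and the definition of the per-protocol set. The non-ovarian 6-month primary endpoint stands.

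The counts assume four-weekly dosing without delays, a month read as a four-week cycle in the dosing text, and a 12-month initial period that ends at Week 48 as the retreatment course does. How many patients would be affected cannot be estimated from the article.

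**What to change.** Study procedures, Durvalumab + tremelimumab combination therapy, Treatment duration and criteria for retreatment, and exclusion 25 in Table 2 must be reconciled so that the protocol contains:

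- one initial treatment period, used in both the dosing and the retreatment text;
- one statement of whether retreatment doses count toward the 24/36 maximum;
- one list of the eligibility criteria that are re-checked at retreatment or continuation, making clear how exclusion 25 applies to study treatment.

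The sponsor's clinical team decides the content; this review takes no view on which duration or retreatment rule is right. Once it is settled, the number of planned doses behind the per-protocol population and the end-of-treatment date that starts the 24-month follow-up should be stated to match.

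The cost is amendment text and a clarification letter to sites. The sample size and the 6-month analysis do not change.
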